### Data Sources

This study will analyze the final datasets derived from the integration of several datasets provided by the Jakarta Provincial Health Office, Ministry of Health, and Social Security Agency on Health after April 2022 (Table 1). Variables such as ID number and date of birth will be used for the dataset linkage (Figure 2). From the New All Records (NAR) and Suspect and Probable (SUSPROB) datasets, symptomatic people with a positive or negative first RT-PCR test result within each of the periods of interest will be identified as cases or controls. Furthermore, people identified as cases will be linked to the entries in the REV POS dataset to extract the outcome of their disease course (Figure 2). People with incomplete data for ID number, date of birth, gender, swab collection date, PCR test result, domicile address, outcome, and date of death (if the case ends in death) will be excluded from further data linkage.

**Table 1 table1:** List source for merged datasets.

Name	Developer	Description	Variable identified
NAR^a^	Ministry of Health Republic of Indonesia	Record of all RT-PCR^b^ SARS-CoV-2 tests carried out by affiliated laboratories	Name ID number Date of birth Sex (male, female) Comorbidity Domicile address Laboratory name Reason for testing Swab collection date RT-PCR result confirmation date RT-PCR testing result
SUSPROB^c^	Jakarta Provincial Health Office	Record and follow-ups of all people with influenza-like illness or probable COVID-19	Name ID number Date of birth Sex (male, female) Comorbidity Domicile address Presence of influenza-like illness (fever, chill, cough, etc) Date of symptom onset Travel history Plan swab testing date Swab collection date RT-PCR testing result
REV POS	Jakarta Provincial Health Office	Records and follow-ups on all positive cases in Jakarta	Name ID number Date of birth Sex (male, female) Comorbidity Domicile address Date of swab collection Case severity (asymptomatic, mild, moderate, severe) Outcome (survived or death) Date of death
PCARE^d^ Vaksin	Social Security Agency on Health Indonesia (BPJS Kesehatan)	Record of all administered COVID-19 vaccines and their recipients	Name ID number Date of birth Sex (male, female) Domicile address Occupation or vaccination batch group (health workers, government officials, elderly, children, civilians) Name of health care facility/vaccination center Vaccination date Vaccination ticket number Vaccination dose Vaccine name Vaccine batch/lot number
Variant dataset	Jakarta Provincial Health Office	Sequencing and genotyping results of the randomly picked positive SARS-CoV-2 samples in the Jakarta area	Sample registry number Date of sample collection Name of the sender laboratory Date of the sample arrival at sequencing lab Name of the sequencing lab Date of the sequencing test Date of result confirmation Variant of SARS-CoV-2

^a^NAR: New All Records.

^b^RT-PCR: reverse transcription polymerase chain reaction.

^c^SUSPROB: Suspect and Probable.

^d^PCARE: Primary Care.

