### Study Participants

The study will include people 18 years or older who domiciled in Jakarta and underwent an RT-PCR test for SARS-CoV-2 infection due to symptoms of influenza-like illnesses within 10 days of the test date. Although people may have more than one RT-PCR result during the period of interest, this study will only account for the first positive or negative result per person as the index test date for each of the COVID-19 waves. People who had at least one sample with a positive SARS-CoV-2 RT-PCR result during the period of interest will be classified as cases, while people with a negative SARS-CoV-2 RT-PCR without any positive results over the period of interest will be classified as controls.

People with a positive RT-PCR test result within 90 days of the preceding index test date, with inconclusive RT-PCR results, who received different vaccines for dose 1 and dose 2 or a heterologous primary vaccine series, or who had a time interval between dose 1 and dose 2 that was less than the government recommendation (<21 days for Pfizer and Sinopharm, <28 days for CoronaVac and Moderna, and <12 weeks AstraZeneca) will be excluded from the analysis. We will also exclude people with incomplete vaccination records, such as people who declared receiving 2 vaccine doses without being able to verify the previous dose.

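### Test-negative people are not described as being checked against REV POS, so a same-wave positive recorded or linkable only there could leave someone in the control group against the plan's own definition

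*Protocol article*

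**What the plan says.** All references are to the protocol article.

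- **Study Participants, control definition:** "people with a negative SARS-CoV-2 RT-PCR without any positive results over the period of interest will be classified as controls".
- **Study Participants, case definition:** "People who had at least one sample with a positive SARS-CoV-2 RT-PCR result during the period of interest will be classified as cases".
- **Study Participants, index rule:** "this study will only account for the first positive or negative result per person as the index test date", applied separately to each wave.
- **Data Sources, assignment of status:** cases and controls are identified from NAR and SUSPROB as "symptomatic people with a positive or negative first RT-PCR test result within each of the periods of interest". The condition that a control has no positive in the wave is not repeated here.
- **Data Sources, use of REV POS:** "people identified as cases will be linked to the entries in the REV POS dataset to extract the outcome of their disease course".
- **Table 1, coverage of each source:** REV POS is "Records and follow-ups on all positive cases in Jakarta". NAR holds the "SARS-CoV-2 tests carried out by affiliated laboratories". SUSPROB is the "Record and follow-ups of all people with influenza-like illness or probable COVID-19".
- **Table 1, fields:** all three list ID number, date of birth and swab collection date. NAR and SUSPROB list an RT-PCR result, and SUSPROB lists symptom onset. REV POS lists neither test type nor onset date.

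**The concern.** The control definition requires a person to be free of any positive over a whole wave. That can only be verified in the sources that are searched. As described, control status is settled in NAR and SUSPROB. REV POS, which Table 1 describes as covering every positive in the city, is used afterwards, for people already called cases, to obtain their outcome.

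Two routes could leave a person with a same-wave positive among the controls:

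1. The positive is in REV POS but in neither NAR nor SUSPROB, for example because the laboratory was not affiliated.
2. The positive is in NAR or SUSPROB but without a usable identifier. Data Sources drops entries with incomplete ID number or other key fields and uses only national identity numbers. The same person's negative entry may be complete, and REV POS may hold the positive with a usable number.

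The first-result wording adds an ambiguity. Read literally, a person who tests negative and later positive in the same wave is a control under Data Sources and a case under Study Participants.

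Where such a person is a true case, for instance after a false negative early in the same illness, the vaccinated share of the controls moves toward that of the cases and VE is understated. Table 3 treats outcome misclassification as controlled by restricting to RT-PCR. The choice of test does not address a positive missed through linkage.

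**Working it through.** **Inputs.** The Sample Size section gives coverage of 20% to 90%, VE of 50% to 90%, precision of ±5%, and 5000 cases with 10,000 controls per brand-and-dose analysis. The Statistical Analysis section sets VE = 1 − OR. The share f of controls who are really cases is not in the document. It is an assumption, taken here as 1% to 10%.

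**The plan's own figure.** The article gives no figure for contamination of controls. As a check that its inputs are read correctly, its sample size was reproduced. With p0 the coverage in controls and p1 = OR·p0/(1 − p0 + OR·p0) the coverage in cases:

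cases = (1.96·OR/0.05)² × [1/(p1(1 − p1)) + 1/(2·p0(1 − p0))]

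At VE 50% and coverage 20%, p1 = 0.1/0.9 = 0.111. The first factor is 19.6² = 384.16 and the bracket is 10.125 + 3.125 = 13.25, which gives 5,090 cases. With 10,180 controls the total is 15,270, against about 15,000 stated. The sample size is not in dispute.

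**Effect of contamination.** If a share f of controls has the coverage of cases, the observed control coverage is

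pc = (1 − f)·p0 + f·p1

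and observed VE = 1 − [p1/(1 − p1)] / [pc/(1 − pc)].

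Example with VE 70%, coverage 90%, f = 10%:

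- p1 = 0.27/0.37 = 0.730
- pc = 0.810 + 0.073 = 0.883
- odds are 2.70 in cases and 7.545 in controls
- observed VE = 1 − 2.70/7.545 = 64.2%

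Observed VE (%) over the range:

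| True VE | Coverage | f = 1% | f = 2% | f = 5% | f = 10% |
|---|---|---|---|---|---|
| 50 | 20% | 49.7 | 49.4 | 48.6 | 47.1 |
| 50 | 50% | 49.7 | 49.3 | 48.3 | 46.6 |
| 50 | 90% | 49.5 | 49.1 | 47.7 | 45.4 |
| 70 | 20% | 69.8 | 69.5 | 68.7 | 67.4 |
| 70 | 50% | 69.7 | 69.3 | 68.3 | 66.6 |
| 70 | 90% | 69.4 | 68.9 | 67.1 | 64.2 |
| 90 | 20% | 89.9 | 89.8 | 89.4 | 88.8 |
| 90 | 50% | 89.8 | 89.7 | 89.1 | 88.2 |
| 90 | 90% | 89.5 | 89.0 | 87.6 | 85.0 |

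The loss in points is 0.1 to 0.6 at f = 1%, 0.2 to 1.1 at 2%, 0.6 to 2.9 at 5% and 1.2 to 5.8 at 10%. At f = 0 it is nil. In an analysis with 10,000 controls, 1% is 100 people and 10% is 1,000.

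**The case against.** The strongest reply is that REV POS is not needed for most of the rule. NAR and SUSPROB hold negatives and positives with identifiers and swab dates, and SUSPROB is meant to cover the symptomatic population under study. A person with a linkable positive in either source is already a case under Study Participants. This stands. A reader might infer that REV POS is the only register able to enforce the control definition, and Table 1 does not support that. What remains is the narrower group described above, and the document does not say whether anyone is in it.

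Three further points stand in part.

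- A correct negative at the index illness followed by a separate infection later in a three-month wave is not a misclassified index test. It breaches the plan's control definition, but the contamination model should not count it as a hidden case. The figures above apply only to controls who are true cases.
- REV POS lists no test type or symptom onset date and includes asymptomatic people. It can flag a possible breach of the control definition but cannot by itself establish a case.
- The workflow figure is not shown and the article is condensed. The sentence on REV POS states the purpose of one link and does not rule out others, so a check of controls may be described elsewhere. If so, one sentence settles the point.

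**Conclusion.** The point holds in limited form. The text sets a condition for controls and describes an assignment step that does not draw on the register described as listing all positives. Its first-result wording can also be read against that condition. The direction of any resulting bias is toward lower VE.

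The size depends on an unknown share: below 1 point at 1%, and up to 5.8 points at 10% in the worst combination (VE 70%, coverage 90%). The calculation is for a crude odds ratio and assumes that the affected controls have the vaccination odds of cases.

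Two stronger conclusions are tempting and are not supported. One is that every wave, brand and dose contrast is biased: if no such people exist, there is no bias. The other is that the loss matches the planned ±5-point precision. Of the nine combinations, only one exceeds 5 points, and only if one control in ten is a true case missed in both test datasets. A second, VE 90% at 90% coverage, reaches 4.97. Nothing in the document points to a share that high. A material bias is therefore possible but not shown, and the case for change rests on its low cost and on consistency with the plan's own definition.

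**What to change.** In Data Sources and the workflow:

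1. Before confirming control status, link test-negative people to REV POS by ID number and date of birth.
2. Exclude from the controls anyone with a REV POS swab date in the same wave. Do not reclassify that person as a case unless NAR or SUSPROB confirms the RT-PCR result and the symptom-date criterion.
3. Report the number removed, by wave. This replaces the assumed share with an upper bound on the contamination that REV POS can reveal.
4. Reword the first-result sentence so that it matches Study Participants: any positive in the wave rules out control status, and the first negative is the index test only for people with no positive.

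The cost is one extra join on a register and identifiers already held, a few lines of protocol text, and probably a small loss of controls. The planned sample size does not change.

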### Study Variables

The primary outcome in this study is symptomatic SARS-CoV-2 infection, defined as a positive RT-PCR test within 10 days from the onset of influenza-like illness. The secondary outcome in this study is fatal SARS-CoV-2 infection, defined as death within 30 days after a positive RT-PCR test result [24]. Meanwhile, the primary exposure in this study was vaccination status, which can be classified as unvaccinated, dose 1 or partial vaccination, dose 2 or primary vaccination, and booster dose. People without any vaccination entries after data linkage with the PCARE Vaksin dataset at the end of each period of interest will be classified as unvaccinated persons. For vaccinated people, we will only consider the last vaccination data entry that happened before the patients’ index RT-PCR test date.

Several covariates should be assessed as potential confounders in the study, such as age in years at the index test date, gender, calendar week of the RT-PCR collection during the period of interest, living in impoverished neighborhoods, presence of any comorbidities, occupation, and reinfection status. The calendar week of the RT-PCR collection during the period of interest will be presented as a whole number starting from week 1 as the start of the period of interest. Living in an impoverished neighborhood will be presented as a dichotomous variable. People will be classified as living in an impoverished neighborhood if their neighborhood number at the subdistrict level is listed as one of the impoverished neighborhoods in the 2018 Jakarta Governor’s regulation concerning improving the quality of settlements in residential areas. Occupation will be presented as categorical variables that consist of health care worker, public or government official, and civilian. Reinfection or people with previous SARS-CoV-2 infections will be presented as a dichotomous variable. People with a previous positive RT-PCR SARS-CoV-2 result that occurred more than 90 days after the current case will be classified as people with a previous SARS-CoV-2 infection [25].

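### The completeness filter requires a survival outcome held only for positive cases, so cases the primary analysis could use are dropped, with a possible but unquantified effect on vaccine effectiveness

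*Protocol article*

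**What the plan says.** Four statements in the protocol article bear on this point.

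- **Who is a case or a control.** Data Sources takes this from the NAR and SUSPROB datasets, where "symptomatic people with a positive or negative first RT-PCR test result within each of the periods of interest will be identified as cases or controls".
- **Where the disease outcome comes from.** The same section says that "people identified as cases will be linked to the entries in the REV POS dataset to extract the outcome of their disease course". Table 1 describes REV POS as "Records and follow-ups on all positive cases in Jakarta", and its row is the only one that lists "Outcome (survived or death) Date of death".
- **The completeness rule.** The required fields include "swab collection date, PCR test result, domicile address, outcome", and the sentence ends "outcome, and date of death (if the case ends in death) will be excluded from further data linkage". The test result and the outcome are separate items, so the outcome meant here is survival or death.
- **The endpoints.** Study Variables gives the primary outcome as symptomatic infection, "defined as a positive RT-PCR test within 10 days from the onset of influenza-like illness". The secondary outcome is death within 30 days of a positive test.

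Linkage to the vaccination register (PCARE Vaksin) is described after the completeness rule. The matched set is then drawn from the resulting final dataset.

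**The concern.** The primary endpoint is fully determined by symptoms, their date of onset and the test result. A symptomatic person with a positive test whose survival status was never recorded, or who died without a recorded date of death, is a valid primary case. The rule still removes that person. Controls have no REV POS entry, so the requirement cannot sensibly apply to them.

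Two things are at stake. The first is certain: any case that fails the rule is lost to the primary analysis without need. The second is conditional: if recording of outcome among cases is related to vaccination, the vaccinated share of the retained cases is distorted and the odds ratio with it. A larger sample does not reduce an error of that kind. The excluded people never reach the vaccination linkage, so the data needed to detect it would not be assembled. Table 3, which lists the potential biases, does not mention this one.

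**Working it through.** **1. Scope of the rule, from the text.** The outcome appears in Table 1 only for REV POS; only cases are linked to REV POS; case and control status needs only NAR and SUSPROB. Hence only cases can fail the outcome requirement. No passage confines the requirement to the death analysis.

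**2. The yardstick.** Sample Size states a precision of ±5%, type 1 error 0.05, anticipated VE 50%–90%, coverage 20%–90%, and about 5000 cases with 10,000 controls. To confirm that ±5% means 5 VE points either side, take the most demanding corner (VE 50%, coverage 20%, two controls per case):

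- OR = 0.5; coverage in controls p0 = 0.20; coverage in cases p1 = 0.5 × 0.20 / (0.80 + 0.5 × 0.20) = 0.111.
- Cases = [1/(p1(1 − p1)) + 1/(2·p0(1 − p0))] × (1.96 × OR / 0.05)² = (10.125 + 3.125) × 384.1 ≈ 5090.

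This agrees with the stated 5000 to within 2%, so 5 VE points is the plan's own margin.

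**3. Effect of losing cases.** Let s_v and s_u be the shares of vaccinated and unvaccinated cases that are retained. Controls are untouched, so

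observed OR = true OR × (s_v / s_u), and observed VE = 1 − (1 − true VE) × (s_v / s_u).

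The documents give no rate of missing outcome, so the ratios below are assumptions chosen to show sensitivity.

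| Retention ratio s_v / s_u | True VE 50% | True VE 70% | True VE 90% |
|---|---|---|---|
| 1.00 (equal loss) | 50% | 70% | 90% |
| 0.90 | 55% | 73% | 91% |
| 1.10 | 45% | 67% | 89% |

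For example, at true VE 70% and ratio 0.90: 1 − 0.30 × 0.90 = 0.73.

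**4. The same in loss rates (also assumed).** At true VE 50%:

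- 10% of vaccinated and 5% of unvaccinated cases dropped: 1 − 0.5 × 0.90/0.95 = 52.6%.
- 20% and 10% dropped: 1 − 0.5 × 0.80/0.90 = 55.6%.
- 10% and 20% dropped: 1 − 0.5 × 0.90/0.80 = 43.8%.

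The 20% and 10% pair gives 73.3% at true VE 70% and 91.1% at true VE 90%.

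**5. What this formula leaves out.** It is unadjusted, whereas the plan reports an adjusted odds ratio. The ratio s_v / s_u should therefore be read as the difference in retention that remains within levels of the matching factors and the covariates in the model.

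**The case against.** The strongest reply is that losing cases only, and not controls, is not in itself a bias: equal loss in vaccinated and unvaccinated cases leaves the odds ratio unchanged. That stands. A reader might infer that the rule selects cases by vaccination status and inflates VE, for instance because mild vaccinated cases are followed up less. The documents contain nothing on follow-up by severity or by vaccination. Poorer follow-up of unvaccinated people would push the estimate the other way.

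Part of any difference would also be absorbed. Age, gender and calendar week are matched. Impoverished neighbourhood, comorbidity and occupation are candidate covariates. If loss of cases depends only on factors in the model, the adjusted estimate is not biased. This also stands, although a candidate covariate helps only if the model building keeps it, and loss related to vaccination in other ways is not covered.

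REV POS is said to cover all positive cases, so the loss may be small. That is fair, but a rule excluding incomplete outcomes presupposes that some exist.

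Study Objectives describes the primary objective as covering mild, moderate and severe disease, and severity is held only in REV POS. Severity is not among the fields the rule requires, however, and the endpoint definition in Study Variables does not use it.

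Finally, the workflow figure and appendix tables are not available here and might restrict the rule. If they do, the unconditional sentence in Data Sources should be brought into line with them.

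A literal reading under which every control is excluded is not tenable: the date-of-death item is itself worded for cases, and the design needs controls.

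**Conclusion.** The point holds as an unnecessary exclusion with a conditional risk of bias, and it should be fixed. It is established from the text that the rule asks for a variable the primary endpoint does not need, that only cases can fail it, and that it acts before vaccination status is linked. It is not established that missing outcome differs by vaccination status, so neither the presence nor the direction of bias in the primary VE can be asserted.

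The possible size depends on true VE. A residual 10% relative difference in retention uses up the whole ±5-point margin at VE 50%, the bottom of the anticipated range, but shifts the estimate by only 1 point at VE 90%. These figures rest on assumed retention ratios. What makes the point worth acting on is that the plan as written leaves the analyst unable to tell which case applies.

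**What to change.** In Data Sources, remove outcome and date of death from the list of fields whose absence excludes a person from the final dataset and the primary analysis. Require them only for the analysis of death within 30 days. Carry all otherwise eligible cases through the vaccination linkage, and report the proportion of cases with a recorded outcome by vaccination status.

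The cost is one sentence and a re-run of the linkage filter. No new data are needed, and cases are gained rather than lost. The article reports that analysis is still under way.

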**Figure 2 figure2:**
[figure not shown]
Study workflow. PCare: Primary Care.

People with data linked to the entries within the Primary Care (PCARE) Vaksin dataset will be classified as vaccinated people (Figure 2). To avoid misclassification of foreigners as unvaccinated people, the study will only use entries with national identity card numbers as ID numbers from each of the study datasets. Vaccinated people with incomplete data on vaccination date and vaccine name will be excluded from the final dataset (Table S2 in Multimedia Appendix 1). From the final dataset, a subset of data containing the matched cases and controls will be created (Table S3 in Multimedia Appendix 1).

As genomic testing was not routinely performed in Indonesia, no data linkage will be performed on the variant dataset. In contrast, the variant dataset, which consisted of the genomic test result of the randomly sampled specimen from the population, will be used to confirm the dominant SARS-CoV-2 variant in Jakarta during each period of interest.

